### Power Analysis and Sample Size Justification

To ensure we have adequate power to detect a difference in our primary outcome, the Social and Occupational Functioning Assessment Scale (SOFAS), we conducted a power analysis. Assuming a significance level of 0.05, a mean SOFAS score of 44.6, and a SD of 15, with 50 veterans, we will have 82% power to detect a significant interaction between time and treatment assuming no change over time in the sham-iTBS group and a change of 13 points in the active iTBS group [90]. On the basis of similar studies of iTBS protocols for patients with depression and PTSD, receiving treatment of similar duration, attrition rates are expected to be low—under 10% [58,90,91]. As such, we plan to enroll participants to ensure we have an adequate sample size considering 10% attrition. Thus, our total sample size will be 56 with 28 in the active iTBS group and 28 in the sham iTBS group.

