Eligibility measures and information collected during the preenrollment phone screen administered by authorized clinical researchers include The Ohio State University TBI Identification Method [92], the Columbia Suicide Severity Rating Scale [89], the UPPS-P [41], self-reported age, the ability to read and speak English, the Center for Magnetic Resonance Research safety form (Multimedia Appendix 2), and TMS safety form (Multimedia Appendix 4). If deemed eligible, participants will be asked to complete an in-person screening.

The in-person screening will consist of completing additional assessments to ensure eligibility and baseline characteristics. They include the structured diagnostic interview from the symptom attribution and classification algorithm, created by individuals involved in this study to determine likelihood and severity of prior TBIs [88], the Neurobehavioral Symptom Inventory, to determine TBI-related symptom presence [98], the Clinician-Administered PTSD Scale for DSM-5 to determine preexisting diagnosis of PTSD [99], the Alcohol Use Disorder Identification Test-Consumption Questions to determine if an alcohol use disorder is present [101], the Drug Use Disorders Identification Test to determine if a drug use disorder is present [102], and the Structured Clinical Interview for DSM-5–Research Version to determine the presence of other psychiatric disorders [104].

Once the listed diagnostic and screening measures are completed and participants meet eligibility criteria, participants will be asked to complete self-reported measures at their baseline, midpoint, and end point visits (Table 1).

Feasibility completion rates will be described according to the reasons participants did not complete the 2-week intervention and the rates of missed sessions. Study completion is defined as completing all 10 sessions. Safety measures will follow procedures used in prior TMS studies [125] and will be scored using the *Medical Dictionary for Regulatory Activities*. Side effects, AEs, and the TMS data safety sheet will assess change severity throughout the intervention. Tolerability will be measured through the number of patients who complete the treatment course and via self-report.

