The study will take place at the Edward Hines, Jr. VA Hospital in Hines, Illinois, a full-service, tertiary-care hospital. Our laboratory is located within the rapid response area, meaning a team of specialized nurses and doctors can be called at any time to emergently assess a patient, should the need arise. Participants will be clinically monitored for seizure by trained research staff. In the event of a seizure, the research team member will call the on-site rapid response team (RRT) to provide emergent medical care to the participant. Cardiopulmonary resuscitation–trained research staff will assess the participant’s airway, breathing, and circulation until the RRT team arrives. RRT will then take over the participant’s care, including administering seizure-abating medications and airway protection, and transport the participant to the emergency department. Any seizure will result in stopping the intervention and withdrawal from the study.

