After the MRI and MT have been completed, participants will be randomized, and the intervention will begin (visits 4-13). Intervention sessions will occur once daily for 10 business days, with each session lasting 30 minutes to 1 hour. Research staff will complete a TMS safety rating scale before and after every iTBS session to assess for changes from baseline for vital signs, sleep duration, fatigue level, recent seizures, and tinnitus. Pain and tolerability measures will be completed at the end of every session to assess daily pain and session tolerability. After iTBS session 5 (visit 8), each participant will be asked to complete the self-report rating scales and neurocognitive testing they completed at baseline.

All veterans who have completed the iTBS treatment course of 10 sessions will be asked to return to the University of Illinois, Chicago’s Center for Magnetic Resonance Research to obtain a second resting-state fMRI for their final research visit. Posttreatment MRI data collection is expected to be completed 72 hours after the iTBS course. This time spacing between stimulation and imaging has been done in similar studies [78] and is thought to be a long enough gap post-iTBS completion not to represent the immediate effects of the most recent stimulation.

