### Limitations of the Study

There are several limitations to consider. The small sample size reduces the study power, which may limit the detection of statistically significant outcome differences. However, this sample size reflects the pilot nature of the study and funding mechanism. Variability in the baseline characteristics of the patient population (ie, co-occurring psychiatric and somatic conditions, coadministration of other medications, etc) that are being studied in detail in this project may impact our findings. Covariates will be explored; however, given the small sample size, only select covariates can be added to the final models. The relatively short follow-up time of 72 hours after the final iTBS treatment will not provide insight into the long-term effects of our intervention. Future studies would benefit from additional follow-up outcomes assessments and imaging several months after the treatment to assess the intervention’s durability. Although prior studies used a dose of 110% MT and a time frame of 10 sessions, we are still determining if these parameters are optimal. A future dosing study would help optimize the treatment parameters. This study does not select targets based on resting-state data; however, in collecting these data in tandem using neuronavigation, we can potentially target more specific sites in the future.

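### Only veterans who complete all 10 sessions are asked back for the second fMRI, so the active-versus-sham connectivity comparison is restricted to completers as written

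*Protocol article*

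**What the plan says.** Study Procedures describes 14 visits. Stimulation occupies visits 4 to 13, so visit 14 is the only one left after the course. For that visit the article says: "All veterans who have completed the iTBS treatment course of 10 sessions will be asked to return" to the imaging centre for a second resting-state fMRI, expected 72 hours after the course.

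The Data Collection section supplies the threshold: "Study completion is defined as completing all 10 sessions". The same section describes self-reported measures at baseline, midpoint and end point, with no completion condition attached. Table 1 lists the Social and Occupational Functioning Assessment Scale (SOFAS, the primary outcome), the suicidality scales and the impulsivity scale under the baseline, midpoint and follow-up assessments. The limitations paragraph refers to "The relatively short follow-up time of 72 hours after the final iTBS treatment".

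The sample size section sets 50 participants for 82% power on SOFAS, states that "attrition rates are expected to be low" (under 10%), and enrols 56. It does not say what counts as attrition.

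**The concern.** Being invited to the second scan depends on completing treatment, which is observed only after randomisation. A participant who stops early or misses one session is randomised but, as the text stands, is not asked to have the second scan. Stronger connectivity in the active arm than in the sham arm is one of the article's hypotheses, and there is no midpoint scan to fall back on. If stopping is related to the arm and to prognosis, the completers in the two arms are no longer comparable, and no analysis plan can recover scans that were never taken.

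A second question is whether the end point SOFAS, suicidality and impulsivity scales share this restriction. The text leaves that open. If they do, the primary comparison faces the same selection, and a 10% allowance may be too small for a rule that a single missed session can break.

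**Working it through.** **1. Imaging: what follows from the text alone.**
- Invitation to the second fMRI: those who completed the 10-session course (Study Procedures).
- Completion: all 10 sessions (Data Collection).
- Other post-treatment imaging visit: none described; 14 visits, with sessions at visits 4 to 13.
- Result: a before-and-after scan pair is planned only for completers, so the connectivity comparison is restricted to them. No assumption is needed for this step.

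**2. Clinical scales: what the text does and does not settle.**
- Pointing towards the 72-hour visit: Table 1 labels the last assessment as follow-up, and the limitations paragraph gives 72 hours as the study's follow-up time.
- Pointing away: the sentence on returning names only the fMRI; the end point measures carry no completion condition; the midpoint scales are asked of each participant at a treatment visit (visit 8).
- Result: a shared restriction is plausible but not stated.

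**3. The plan's own sample size.** 50 / (1 − 0.10) = 55.6, rounded up to 56. This reproduces.

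**4. The plan's own power.** Inputs are "Assuming a significance level of 0.05, a mean SOFAS score of 44.6, and a SD of 15", and "assuming no change over time in the sham-iTBS group and a change of 13 points in the active iTBS group". Two-sided testing is assumed. For n analysed in equal arms, the noncentrality is 13 / (s × √(4/n)), where s is the SD of change, with n − 2 degrees of freedom.
- With s = 15 and n = 50, noncentrality is 3.06 and power 85.1%, not 82%.
- If 15 is the SD of a single score, s = 15 × √(2(1 − ρ)). At ρ = 0.46, s = 15.6, noncentrality is 2.95 and power about 82%.
- The article gives no ρ, so s = 15.6 is fitted to reproduce the stated 82%.

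**5. Illustration for SOFAS.** This assumes that non-completers lose the end point SOFAS, that misses are independent across sessions and that there are no make-up sessions. With per-session attendance p, the completing fraction is p^10.
- For 90% to complete: p = 0.9^(1/10) = 98.95%. For exactly 50 of 56: (50/56)^(1/10) = 98.9%.

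| Attendance per session | p^10 | Remaining of 56 | Power at s = 15.6 |
|---|---|---|---|
| 98% | 0.817 | 45.8, about 46 | about 79% |
| 97% | 0.737 | 41.3, about 41 | about 74% |
| 95% | 0.599 | 33.5, about 34 | about 65% |

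**6. Sensitivity to the assumptions.** If absences cluster in six people, 50 completers remain at quite different overall attendance out of 560 sessions:
- six attend nothing: 500/560 = 89.3%;
- six stop after session 5: 530/560 = 94.6%;
- six miss one session each: 554/560 = 98.9%.

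If the SD of change is 15 rather than 15.6, 46 completers still give about 82% power.

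**The case against.** The sentence on returning is about the fMRI, and so is the 72-hour interval in Study Procedures. The power calculation concerns SOFAS. A reader might infer that the primary comparison becomes a completers analysis and that the design needs 99% attendance. The article supports neither: it sets no completion condition for the end point scales, names no completers population, and says nothing on make-up sessions or the pattern of absences. The visit diagram that might place the scales is not reproduced in the text available. If attrition means failing to complete the course, the 99% figure merely restates the 10% allowance. The completion definition sits among the feasibility measures and is not an analysis-inclusion rule. This objection stands, which is why the SOFAS figures are conditional.

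A reader might also infer that tolerability information on those who stop is lost. It is not: the Analytic Plan computes feasibility, safety and tolerability statistics for all participants, and pain and tolerability are recorded at every session. Nor do the documents show that active participants stop more often. The sham is designed to mimic the sensation of active stimulation, so arm-dependent stopping is a possibility only. The seizure rule, "Any seizure will result in stopping the intervention and withdrawal from the study", is a safety provision and adds nothing to an argument about missed sessions.

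The objection does not reach the imaging. Leaving analysis sets to a fuller document is normal for an article, but this is a stated rule about whose data are collected.

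**Conclusion.** The point holds for connectivity: followed literally, the article gives a second scan only to participants who complete all 10 sessions, so that comparison is not one of all randomised participants. The size and direction of any bias cannot be calculated, because the documents give no stopping rates by arm and no connectivity effect size.

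For SOFAS, suicidality and impulsivity the restriction is possible but unconfirmed. Remaining numbers of about 46, 41 and 34, with power near 79%, 74% and 65%, apply only if those scales are lost for non-completers, misses are independent, there are no make-up sessions and the SD of change is about 15.6. The 98%, 97% and 95% attendance rates are assumed. The correction is cheap and best made early, since the article reports two participants enrolled as of July 2024; it does not show that the primary analysis is invalid.

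**What to change.** In Study Procedures, state that all randomised participants are asked to return for the end point scales and the second fMRI about 72 hours after their last session, or last scheduled session, regardless of how many sessions they received. This also settles where the end point scales are taken.

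In the Analytic Plan, state that SOFAS and connectivity are analysed by assigned arm in all randomised participants with data, with all-10-session completers as a sensitivity analysis. In the sample size section, define the 10% attrition as missing end point data rather than missed sessions. The rules for stopping treatment and the seizure rule stay as they are.

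The cost is protocol wording and a few more end point visits and scans: about 6 participants if the plan's own allowance is right (56 − 50), all at a visit type already in the schedule. The effect estimate may be somewhat smaller, because participants with partial treatment are included.

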### Analytic Plan

A statistical significance level corresponding to α=.05 will be used to test hypotheses.

Descriptive statistics of feasibility, safety, and tolerability measures will be computed for all participants and compared between active- and sham-iTBS groups. We will calculate the categorical variables’ frequencies and compare them using chi-square analyses for the descriptive statistics [126]. For the continuous variables (ie, daily pain ratings), we will compute mean, median, range, and SDs and compare using 2-tailed *t* tests.

For functional outcome measures, we will estimate a mixed model ANOVA to measure differences within-participants (how the SOFAS changes over time), between-participants (how the SOFAS differs between active and sham iTBS), and whether there is a significant interaction between time and treatment [127]. We will assume equal variance between test and control groups [128]. If the variance is unequal, we may transition to a generalized linear mixed (GLM) effects model [129].

For our neuroimaging analysis, to evaluate the VMPFC to the amygdala and anterior cingulate relationships and how they change before and after treatment, we will define ROIs for the amygdala and anterior cingulate with clear anatomical boundaries identified using Freesurfer [130]. Average time-series data will be extracted, and GLM will be used to quantify the relationship between the seeds and targets. The GLM results will yield individual *r* values (ie, correlations), which will be normalized into *Z* scores using Fisher R-to-Z transformation [131]. The individual maps of *Z* scores will be the primary measure of connectivity between the seed and target ROIs. We will then implement an ROI-to-ROI analysis within the connectivity toolbox to evaluate resting-state functional connectivity between the amygdala, anterior cingulate, and VMPFC [132]. We will assume a normal distribution and use Fisher’s *Z* test to compare active-iTBS and sham-iTBS groups, both before and after treatment [133]. We will adjust for a priori covariates, including age, sex, and baseline psychiatric diagnoses. All analyses will be corrected for multiple comparisons using false-discovery rate correction. We will use linear mixed models to test how connectivity changes correspond to functional and mental health outcome changes, with functional and behavioral measures included as the dependent variables [134].

To inform future research studies, we will estimate regression models that include additional covariates such as demographics, psychotropic medication use, comorbid psychiatric diagnoses, and scores on the Inventory of Depressive Symptomatology, Self-Report and the PTSD Checklist for DSM-5, in addition to testing our hypotheses for the primary and secondary outcomes.

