### Hypotheses

Our central hypotheses are that frontal pole iTBS will be safe, feasible, and tolerable among veterans with mTBI based on existing literature that suggests frontal pole iTBS is as safe and tolerable as iTBS performed elsewhere [23,25,62]. Similarly, iTBS, when administered to individuals with mTBI is as safe and tolerable as in individuals without mTBI [63]. Given that we are using an established iTBS protocol within the established TMS safety guidelines [84], we do not anticipate significant AEs.

We further hypothesize that social and occupational functioning, negative urgency impulsivity, and SI will be improved for individuals who receive active-iTBS compared with those who receive sham-iTBS. Even if only a single domain improves, we consider this a positive finding.

In addition, we hypothesize that resting-state functional connectivity between the VMPFC and the limbic system (especially the amygdala and anterior cingulate cortex) will be strengthened for the active-iTBS group compared with the sham-iTBS group. We also expect that veterans with increased connectivity between these regions of interest (ROIs) will likely show the most functional improvements.

Pending the results of this pilot trial, larger-scale RCTs may be warranted to establish the efficacy of frontal pole iTBS for social and occupational functional deficits, negative urgency impulsivity, and SI.

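### The only hypothesis tests named for the central safety, feasibility and tolerability hypotheses are active-versus-sham difference tests, which cannot support them; interval estimates should carry the conclusion

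*Protocol article*

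**What the plan says.** The Hypotheses section states: "Our central hypotheses are that frontal pole iTBS will be safe, feasible, and tolerable among veterans with mTBI". The support offered there is that frontal pole stimulation is as safe as stimulation elsewhere, and that people with mTBI tolerate iTBS as well as people without it. Neither comparator is in this trial; the only control is sham.

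The Analytic Plan opens with "A statistical significance level corresponding to α=.05 will be used to test hypotheses". For the measures at issue it then says "Descriptive statistics of feasibility, safety, and tolerability measures will be computed for all participants and compared between active- and sham-iTBS groups". For categorical measures it will compute frequencies and "compare them using chi-square analyses for the descriptive statistics". For continuous measures, such as daily pain ratings, it will compute mean, median, range and "SDs and compare using 2-tailed *t* tests".

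Other sections add description. Under Data Collection, "Feasibility completion rates will be described according to the reasons participants did not complete the 2-week intervention", together with missed sessions; completion means all 10 sessions, and tolerability is the number completing plus self-report. Under Safety and AE Monitoring, every side effect and adverse event is graded 0 to 5 and reported. Power Analysis and Sample Size Justification addresses only the SOFAS.

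**The concern.** The hypothesis and the test do not match. The hypothesis is an absolute statement about the active treatment. The null hypothesis of the named tests is that active equals sham. Rejecting it would count against safety or tolerability. Failing to reject it is the only result that could seem to agree with the hypothesis, and that becomes more likely as the sample shrinks. Equality with sham is also not the feasibility question: if both arms completed equally badly, the test would show no difference.

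Safety and feasibility are main products of a pilot, and the Hypotheses section makes larger trials depend on its results. A p value above .05 that was read as reassurance would carry that reading forward in a population recruited for recent suicidal ideation.

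**Working it through.** **Inputs from the protocol article.** 28 per arm, from 50 evaluable participants and 10% attrition: 50 / 0.90 = 55.6, rounded up to 56, which reproduces the stated total. Alpha is .05, taken as two-sided for the chi-square test. The stated 82% power concerns the SOFAS and does not bear on this point.

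**Assumption.** The article gives no adverse event rate. Sham rates from 2% to 20%, tripled on active, are used to show a range. The only related figure in the plan is attrition of under 10%, which is not the same as failing to complete all 10 sessions.

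**Step 1: can the test support the claim?** If both arms have the same count, the chi-square statistic is 0 and p = 1, whether completion is 28/28 or 14/28 in each arm. The test carries no information about the active arm's own level.

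**Step 2: power against a tripled rate.** The usual approximation is

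power = Φ{ [ |p1 − p2|·√n − 1.96·√(2·p̄(1 − p̄)) ] / √(p1(1 − p1) + p2(1 − p2)) }, where p̄ is the mean of p1 and p2.

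- 5% v 15%: (0.10 × 5.292 − 1.96 × 0.4243) / 0.4183 = −0.72, power 23%.
- 10% v 30%: (0.20 × 5.292 − 1.96 × 0.5657) / 0.5477 = −0.09, power 46%.
- 20% v 60%: (0.40 × 5.292 − 1.96 × 0.6928) / 0.6325 = 1.20, power 88%.

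Exact power sums the product of the two binomial probabilities over every table with p < .05:

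| Sham v active | Pearson chi-square | Fisher |
|---|---|---|
| 2% v 6% | 5% | 0.3% |
| 5% v 15% | 24% | 8% |
| 8% v 24% | 38% | 22% |
| 10% v 30% | 47% | 33% |
| 12% v 36% | 57% | 44% |
| 15% v 45% | 72% | 61% |
| 20% v 60% | 88% | 82% |

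Power passes 50% at a sham rate of about 11% (Pearson) or 13% (Fisher). Below that, a tripling is missed more often than found: about 76% of the time at 5% v 15%, and about 53% at 10% v 30%.

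**Step 3: continuous measures.** A two-sided t test with 28 per arm has 45% power at a standardised difference of 0.5 and reaches about 81% at 0.77.

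**Step 4: what 28 active participants can show.** Exact (Clopper-Pearson) 95% limits:

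- 0/28 events: upper limit 1 − 0.025^(1/28) = 12.3%.
- 26/28 completing (92.9%): 76.5% to 99.1%.
- 28/28 completing: lower limit 0.025^(1/28) = 87.7%.

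For the arm difference with 10% in each arm, the approximate 95% half-width is 1.96 × √(2 × 0.1 × 0.9 / 28) = 15.7 percentage points.

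**The case against.** The strongest reply is that the plan is already largely descriptive. Frequencies and summary statistics come first, completion is reported with reasons, every adverse event is graded and reported, and the chi-square tests are attached to the descriptive statistics. This stands. A reader might infer that difference tests are the only way these measures are examined; the documents do not support that. They are the only hypothesis tests named for them.

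Three other stronger readings also fail.

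- **That the tests usually miss a tripled rate whatever its level.** No event rate is given, and the statement fails above a sham rate of about 11% to 13%.
- **That the plan sets no feasibility threshold and is therefore in error.** This is a condensed article, and a threshold may stand in the full protocol or analysis plan. Nor can 90% completion be taken as the plan's own criterion. The remark that "attrition rates are expected to be low" is an attrition assumption used to go from 50 to 56. As a success rule for 28 participants it would require 26 completers (25/28 = 89.3%), and it would fail 54% of the time if true completion were exactly 90% (P(X ≥ 26) = 0.459).
- **That the investigators will read non-significance as safety.** No sentence says so. The Conclusions of the Abstract promise only preliminary evidence, and the Limitations concede that the small sample may hide differences. The article does not rule that reading out either, and the alpha statement heading the Analytic Plan exempts no hypothesis.

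**Conclusion.** The point holds in a limited form. The claim that "frontal pole iTBS will be safe, feasible, and tolerable among veterans with mTBI" is absolute, and the inferential method named for it is a test of difference from sham, which cannot support it at any sample size. At 28 per arm the test is also weak for uncommon events: exact Pearson power is 24% for 5% v 15% and 47% for 10% v 30%. For commoner events the power argument falls away (72% for 15% v 45%, 88% for 20% v 60%), but the mismatch between claim and test remains. The power figures rest on assumed event rates, a two-sided uncorrected chi-square test and all 28 per arm being analysed; Fisher's test gives lower power. The planned descriptive reporting is sound and supplies most of what is needed. What should change is the basis on which the conclusions are drawn.

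**What to change.** In the Analytic Plan, state that conclusions on safety, feasibility and tolerability will rest on estimation:

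- for adverse events, serious adverse events, session completion and study completion, each arm's rate with an exact 95% interval;
- the active-minus-sham difference for each, with a 95% interval, and likewise the mean difference for continuous ratings;
- a sentence saying that a non-significant difference from sham is not evidence of safety or tolerability.

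A formal non-inferiority test is not a practical substitute. With 90% completion in both arms, one-sided alpha 0.025 and 80% power, n per arm = (1.96 + 0.84)² × 2 × 0.9 × 0.1 / margin². That is 142, 63 or 36 per arm for assumed margins of 10, 15 or 20 points, all above 28.

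The cost is a few lines of text and a few intervals. Data collection and sample size are unchanged, and only 2 participants had been enrolled as of July 2024. The downside is that the safety and feasibility conclusions become visibly less certain: even an event never seen in 28 active participants would be reported as compatible with a rate of up to 12.3%.

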#### Data Collection

Data collection is expected to take approximately 18 to 20 hours per participant over the intervention period of 2 weeks. Assessments will be collected at 4 time points in the study: screening, baseline, midpoint, and end point (Table 1).

**Table 1 table1:** Assessment timeline and purpose.

Assessment name		Assessment purpose	Items	Scoring	Validity and reliability

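### The primary SOFAS test is a time-by-treatment interaction with no end-point contrast or baseline adjustment and with an optional change of model; a baseline-adjusted end-point comparison would use the same data with more power

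*Protocol article*

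**What the plan says.** The section on power and sample size names SOFAS as the primary outcome. Its inputs are: "Assuming a significance level of 0.05, a mean SOFAS score of 44.6, and a SD of 15, with 50 veterans". With no change in the sham arm and a 13-point change in the active arm, it concludes: "we will have 82% power to detect a significant interaction between time and treatment". Allowing for 10% attrition, 56 are enrolled, 28 per arm.

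The Analytic Plan sets the test: "we will estimate a mixed model ANOVA to measure differences within-participants (how the SOFAS changes over time", plus a between-participants comparison of the arms and the interaction of time with treatment. It assumes equal variance in the two arms and adds: "If the variance is unequal, we may transition to a generalized linear mixed (GLM) effects model". It gives no test or threshold for that step. The general rule is "A statistical significance level corresponding to α=.05 will be used to test hypotheses". Neither section names a primary time point or a baseline SOFAS covariate. The later covariate regressions, meant to inform future studies, do not list baseline SOFAS either.

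On timing, Data Collection says: "Assessments will be collected at 4 time points in the study: screening, baseline, midpoint, and end point". Table 1 places the rater-administered SOFAS at baseline, midpoint and follow-up. Study Procedures describes the midpoint visit, after session 5, differently: "each participant will be asked to complete the self-report rating scales and neurocognitive testing they completed at baseline". It does not mention rater-administered scales there.

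**The concern.** An interaction test with baseline among the outcomes spends information in two ways. With two visits it is a comparison of change scores, which subtracts the whole baseline value instead of the part that predicts the end point. With three visits it becomes an omnibus 2-df test. That test can be significant because of the midpoint alone, and it does not by itself estimate the end-of-treatment difference that readers will look for. In a trial with fewer than 30 per arm, whose own limitations section concedes reduced power, adjusting for a baseline value that is collected anyway is an inexpensive gain.

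The optional switch is a separate weakness. If the primary model may change once the variances have been seen, the primary p value depends on an unstated decision. The alternative named does not match the problem either, since a generalized linear mixed model does not by itself allow a different variance in each arm.

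**Working it through.** **Inputs.** From the power section: alpha 0.05, SD 15, change 13 v 0, 50 evaluable participants, hence n = 25 per arm. Assumptions: two-sided testing, the same SD at every visit, and a within-person correlation ρ, which the article does not give and which is therefore varied. Power is from the noncentral t or F distribution.

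**Enrolment.** 50 / 0.9 = 55.6, rounded up to 56. This reproduces.

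**The stated 82%.** A plain two-group comparison with SD 15 gives 85.1% (t) or 86.5% (normal approximation), not 82%. The interaction over two visits is a t test on change, with

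SD of change = 15 × √(2(1 − ρ)), 48 df.

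Solving for 82% gives ρ = 0.455: SD of change = 15 × √(2 × 0.545) = 15.66, and noncentrality = 13 / (15.66 × √(2/25)) = 2.94.

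**Baseline-adjusted end-point comparison (ANCOVA).** Residual SD = 15 × √(1 − ρ²), 47 df. At ρ = 0.455 this is 15 × √(1 − 0.207) = 13.36, noncentrality = 13 / (13.36 × √(2/25)) = 3.44, and power 92.1%. The variance relative to change scores is (1 + ρ)/2 = 0.73, a cut of about 27%. At this ρ, 19 per arm would already give 82%.

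| ρ | two-visit interaction | baseline-adjusted end point |
|---|---|---|
| 0.3 | 71.8% | 88.2% |
| 0.455 | 82.0% | 92.1% |
| 0.5 | 85.1% | 93.4% |
| 0.7 | 97.2% | 98.8% |

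**Three-visit interaction.** Under compound symmetry, with 2 and 96 df,

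λ = (n/2) × Σ(centred arm differences)² / (15²(1 − ρ)).

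At ρ = 0.455 the denominator is 225 × 0.545 = 122.6.

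- Steady gain (0, 6.5, 13): centred sum of squares 84.5, λ = 12.5 × 84.5 / 122.6 = 8.6, power 73.7%.
- Absent or full midpoint effect (0, 0, 13 or 0, 13, 13): centred sum of squares 112.7, λ = 12.5 × 112.7 / 122.6 = 11.5, power 85.7%.

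A multivariate version of the test gives 72.2% and 84.4%.

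**Can three visits also yield 82%?** Yes. The univariate test reaches 82% at ρ of about 0.55 with a steady gain, or about 0.40 with an absent or full midpoint effect.

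**Sensitivity.** With a first-order autoregressive pattern and the same baseline-to-end-point correlation of 0.455, the multivariate three-visit test has about 72% power for a steady gain and about 93% for an absent or full midpoint effect.

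**The case against.** A time-by-treatment interaction is a valid test, it is the test that was powered, and this is a pilot. All of that stands. The point is one of efficiency and precise specification, not of validity. The gain also shrinks as the correlation rises (99% v 97% at 0.7). Against the three-visit test it depends on the course over time: in the autoregressive check with an abrupt effect, the omnibus test reaches about 93%, level with the adjusted comparison. The 92% is for a pooled-variance ANCOVA. Power for a mixed model with arm-specific variances was not computed.

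Four stronger readings are tempting and are not supported:

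- **That 82% is wrong for three visits.** The article gives neither a correlation nor a midpoint effect, and plausible values of both return 82%. An article may also leave such detail to the full protocol.
- **That the documents contradict each other on whether SOFAS is taken at midpoint.** Table 1 lists it there. Study Procedures fails to mention rater-administered scales but does not exclude them. This is loose wording.
- **That anyone with a missing visit is dropped.** The Analytic Plan specifies no complete-case rule, and a likelihood-based mixed model with these terms would keep partial records.
- **That the arm main effect, which averages in baseline, decides the trial.** The interaction is the powered test.

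Nor was the optional switch shown to lose power or to inflate the type I error by any stated amount.

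**Conclusion.** The concern holds as a choice of analysis that should be improved. With the protocol's own effect, SD and evaluable numbers, a baseline-adjusted end-point comparison is more powerful than the two-visit interaction at every correlation tried: 88% v 72% at 0.3, 92% v 82% at 0.455, and 99% v 97% at 0.7. At 0.455 under compound symmetry it also exceeds the three-visit interaction, which has about 74% to 86%. These figures rest on two-sided testing, equal SDs across visits and an assumed correlation.

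The stated 82% can be neither confirmed nor refuted from the article. The optional change of model is a weakness of prespecification only, with no demonstrated cost in power.

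**What to change.** 1. Make the single primary analysis the arm difference in SOFAS at end point, from a linear mixed model for post-baseline SOFAS with arm, visit, arm-by-visit and baseline SOFAS. If SOFAS is taken only at baseline and end point, this reduces to ANCOVA.
2. Fix the variance structure in advance, for example a covariance estimated separately by arm with small-sample degrees of freedom, and delete the optional switch.
3. Align the midpoint wording in Study Procedures with Table 1, so that it is plain whether SOFAS is rated then.
4. Restate the power for the chosen contrast and model, giving the assumed correlation and a range around it.

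The cost is revised wording, a new power line and a few degrees of freedom, more if variances are arm-specific. No new data are needed. The article reports 2 participants enrolled as of July 2024.
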